#### **Data Collection Procedures**

Children requiring venipuncture will be identified by the nurse in the pediatric unit. If the children meet the inclusion criteria for recruitment, the nurse will refer the children and their accompanying parents/ legal guardians to the RA in the treatment room, who will give them an information sheet, explain the study and show the IVR equipment. If they agree to participate, written informed consent from the accompany parents/ legal guardians and assent from the children will be obtained. The RA will then acquire socio-demographics information from the parents/ legal guardians and clinical characteristics of the children from medical record before randomization. According to the subject allocation scheme, children in the control group will receive standard care, whereas those in the intervention group will additionally receive IVR intervention.

Participants will be assessed:10 minutes prior to the procedure (T0), during the procedure when the needle insert to the skin (T1), immediately after the procedure indicate by application of band aid to the venipuncture site (T2), and 30 minutes after the procedure (T3). At T0, a set of baseline data - saliva sample for a measure of cortisol, FPS-R, VAS for anxiety, CSAS-C, and heart rate - will be collected from the patients by the RA. At T1, heart rate will be obtained. At T2, FPS-R, VAS for anxiety, CSAS-C and heart rate will be obtained from children. At the same time, the RA will record the length of procedure and invite the health care providers involved to fill in the staff satisfaction scale. At T3, saliva sample for a measure of cortisol, FPS-R, VAS for anxiety, CSAS-C, and heart rate will be obtained from patients again. Please refer to table 1 and figure 1.

#### **Ethical consideration**

Ethical approval will be sought from the Research Ethics Committee (Kowloon Central/Kowloon East). Written informed consent from parent/ legal guardians and assent from child will be obtained. Participants and parents/ legal guardians will be informed that the care will not be affected by their participation status.

## **Data analysis**

IBM SPSS 24 will be used for data analysis. Continuous demographic and clinical variables will be presented as their means and standard deviations, whereas categorical data (e.g. sex) will be presented in frequencies and percentages, as appropriate. The intention-to-treat principle will be adopted for the outcome comparisons between the intervention and control groups. The generalized estimating equations (GEE) model will be used to compare each of the outcome measures across the time points between the two groups. GEE model can account for intra-correlated repeated measures data and produce unbiased estimates even if there are missing data, provided that the data are missing at completely random. Cohen's d values will be calculated to estimate the effect sizes of the IVR intervention on the outcome variables. All statistical analyses are two-sided and level of significance will be set at 0.05.

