#### **Sample size – Patients**

In 2016, about 250 hospitalized patients aged between 4 years to 12 years were admitted to the unit and required venipuncture. Sample size estimation was based on the effect estimated from a previous IVR study using the FPS-R Scale as a primary outcome measure [11]. By using the power analysis software, GPower 3.1, it was estimated that a sample size of 85 participants per group would enable a 2-arm RCT to detect a between-group difference of 0.8 in FPS-R scale with a pooled standard deviation of 1.84 with 80% power at 5% level of significance. Taking into account of up to 15% attrition rate [24], 200 children will be recruited. Furthermore, to account for those who fail in the first attempt of venipuncture, the total sample size is adjusted to 250 children to be recruited with the estimation of 20% of unsuccessful cases in the first attempt. As such, the total recruited number of children will be 250 for the experimental and control groups, with 125 children in each group.

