#### **Randomization**

Eligible participants will be randomly assigned in a 1:1 ratio to the intervention group who will receive the IVR intervention or a control group that will receive standard care only using stratified permuted block randomization with a block size of 10 to maintain a good balance of participants between the two groups throughout the subject recruitment period. Randomization will be stratified by age group (4–7; 8–12 years old) in equal numbers.

According to Piaget’s theory, children from 4 years to 7 years of age belong to the same pre-operational stage, whereas those in the age range 8–12 years belong to the concrete operational stage [31]. Children in different stages differently perceive information and pain stimuli sensitivity [32].

A sequence of grouping identifiers (I=intervention group or C=control group) will be prepared in advance by an independent statistician, using computer-generated random codes for each of the two strata of age group. The group identifiers for each age group will then be put in serially numbered sealed opaque envelopes according to the underlying random sequence list by the statistician. The group allocation of the patients will be assigned according their ages, sequence of enrolment in the study, and the group identifier contained in the corresponding numbered envelopes. Group allocation will be concealed from the research assistant (RA), ward staff, child, and parents/ legal guardians until consent and baseline assessment data has been obtained. Given the nature of the intervention, blinding of participants, RA, and health care provider will be difficult. Nevertheless, the lack of blinding will not necessarily contribute to a source of bias because children are unlikely to change their behavior even when they know they are participating in a certain intervention [33].

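### The planned GEE compares the arms over time points that include the pre-intervention T0 and states no baseline covariate; adjusting for T0 would keep power at or above the planned level on any reading

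*Protocol*

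**What the plan says.** The Data analysis section of the protocol names one model for all outcomes: "The generalized estimating equations (GEE) model will be used to compare each of the outcome measures across the time points between the two groups". It names no contrast, no primary time point and no covariate.

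The Abstract lists four evaluation times, the first 10 minutes before the procedure. Data Collection Procedures labels that time T0 and describes its content as "At T0, a set of baseline data", with FPS-R among the items. FPS-R is taken again at T2 (immediately after the procedure) and T3 (30 minutes after). At T1, needle insertion, only heart rate is taken. Under Randomization, allocation stays concealed until the baseline assessment has been obtained, so T0 scores can differ between arms only by chance.

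The Sample size – Patients section plans for 85 children in each arm. The target is given as follows: "detect a between-group difference of 0.8 in FPS-R scale with a pooled standard deviation of 1.84 with 80% power at 5% level of significance". The section mentions no correlation and no repeated measures, and does not say whether 1.84 is the SD of a score or of a change. Change from baseline appears as an effect measure in one place only, the cost-effectiveness ratio under Secondary outcomes.

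**The concern.** The sample size and the analysis describe different comparisons. The calculation is for two independent means at one time. The analysis compares arms over a set of times in which the first cannot carry a treatment effect.

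With T0 as a level of time, a natural test is group-by-time. For FPS-R at T2 that is the arm difference in change from T0. Its variance depends on the T0-T2 correlation, and it exceeds the planned variance when that correlation is low. The other natural test, a group effect averaged over all times, dilutes the effect with a time at which none is possible. Neither uses T0 in the way that gains precision, which is as a covariate.

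At stake is the precision of the primary result. The baseline score is collected anyway, and the plan does not say that it will be used for adjustment.

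**Working it through.** **Inputs from the protocol.** Difference 0.8 and SD 1.84 ("a between-group difference of 0.8 in FPS-R scale with a pooled standard deviation of 1.84"); 85 per group; power and alpha ("with 80% power at 5% level of significance"); two-sided tests ("All statistical analyses are two-sided and level of significance will be set at 0.05"); equal allocation ("Eligible participants will be randomly assigned in a 1:1 ratio"). Allowances: 15% attrition and 20% failed first attempts, giving 125 per group recruited.

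**Assumed, because the protocol gives no figure.** The correlation r between FPS-R at T0 and T2 (0 to 0.5 shown), and the ratio b of the T0 SD to the T2 SD (1 in the table, 0.5 as a variant).

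**Step 1, the plan's own figure.** Standardised effect d = 0.8/1.84 = 0.435. A two-sided two-sample t-test (noncentral t) with 85 per group has power 80.5%, and 85 is the smallest n that reaches 80%. Then 170/0.85 = 200 and 200/0.80 = 250. All the stated figures reproduce.

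**Step 2, SD of each candidate contrast**, taking 1.84 as the SD of a single score:
- Arm difference at T2 alone: 1.84. Power is 80.5% at any r.
- Arm difference in change from T0 to T2: 1.84 × sqrt(1 + b² − 2br), which is 1.84 × sqrt(2(1 − r)) when b = 1.
- Arm difference at T2 with T0 as covariate: 1.84 × sqrt(1 − r²).

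Example at r = 0.3, b = 1: change SD = 1.84 × sqrt(1.4) = 2.18; covariate-adjusted SD = 1.84 × sqrt(0.91) = 1.76.

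**Step 3, power with 85 per arm, b = 1 (noncentral t):**

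| r | Change T0 to T2 | T0 as covariate |
|---|---|---|
| 0 | 51% | 80% |
| 0.1 | 56% | 81% |
| 0.2 | 61% | 82% |
| 0.3 | 66% | 84% |
| 0.4 | 73% | 87% |
| 0.5 | 80% | 90% |

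A simulation of the saturated GEE with robust variance gave 68% for the change contrast at r = 0.3 and 82% at r = 0.5, close to the table.

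**Step 4, how the threshold moves.** The correlation at which the change contrast reaches 80%:
- 85 per arm, equal SDs: 0.49.
- 106 per arm, equal SDs: about 0.36. This is the number if failed first attempts stay in under intention to treat, 250 × 0.85/2 = 106.
- 125 per arm, equal SDs: about 0.25.
- 85 per arm, b = 0.5: the variance factor is 1.25 − r, which equals the planned 1 at r = 0.25. Power is 71%, 75%, 79% and 82% at r = 0, 0.1, 0.2 and 0.3.

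With 106 per arm and equal SDs, the change contrast has 65%, 70% and 76% power at r = 0.1, 0.2 and 0.3, against 89%, 90% and 91% with T0 as covariate.

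**Step 5, the averaged group effect, for illustration.** Assume r = 0.3 between all three times and an effect of 0.4 at T3. The mean effect is (0 + 0.8 + 0.4)/3 = 0.4, the SD of a child's mean is 1.84 × sqrt((1 + 2 × 0.3)/3) = 1.34, and power with 85 per arm is 49%. If the full 0.8 persists at T3, it is 73%.

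**The case against.** The strongest reply is that the protocol says none of this outright. It names a GEE and the time points; it does not say that group-by-time is the test, and it does not rule out a baseline covariate. Contrasts and covariates of a named model are commonly left to a statistical analysis plan, which is not shown here. The arm difference at T2 can be read from the same GEE, has about 80% power at any correlation and matches the sample size section. If 1.84 is already the SD of a change, the stated power holds for a change contrast too.

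A second reply concerns the equal-SD assumption. The protocol reports, for the study behind the sample size, a four-fold rise in control-group pain after the procedure. That suggests low pre-procedure scores on a scale bounded at zero, so a smaller T0 SD is plausible, though no SD is given. A weak T0-T2 correlation is likewise a conjecture that the documents neither support nor exclude.

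All of this stands. A reader might infer from the table that the trial misses its 80% power unless the correlation exceeds 0.5. The documents do not support that: it needs a change contrast, a single-score SD, equal SDs and only 85 analysed per arm, all at once.

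The replies do not touch the remedy. With equal SDs, T0 as covariate beats the change contrast at every correlation below 1. Apart from one degree of freedom, it is never worse than the comparison at T2 alone.

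**Conclusion.** The point holds as a mismatch with a free remedy, not as a demonstrated shortfall in power. The analysis text places T0 among the compared time points and states no adjustment for it, while the sample size assumes a single two-group comparison. The two agree for some contrasts and not for others.

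Under the four conditions together, power is about 51% to 73% for correlations of 0 to 0.4. It recovers at lower correlations if more than 85 per arm are analysed or if T0 varies less than T2, and there is nothing to recover if the contrast is at T2 or if 1.84 is a change SD. The correlation and the SD ratio are assumptions throughout. The gain from the covariate does not depend on which contrast was intended; its size grows with the correlation.

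**What to change.** Amend Data analysis as follows.

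- For outcomes with a T0 value (FPS-R, anxiety, heart rate, cortisol), model only post-baseline values, with the child's T0 value of the same outcome as a covariate.
- Include arm and, where there is more than one post-baseline time, time and arm-by-time. Cortisol has only T3 after baseline, so it needs arm and the T0 value alone.
- Name the adjusted arm difference in FPS-R at T2 as the primary contrast.
- In the sample size section, say whether 1.84 is the SD of a score or of a change.

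The cost is a few sentences. T0 is already collected, no extra children or measurements are needed, and the sample size can stay as it is.

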#### **Implementation Protocol**

The venipuncture procedure will be conducted in the treatment room while parents/ legal guardians wait outside. Patients assigned to the intervention group will receive IVR intervention prior to the start of venipuncture until the end of the procedure [11, 23]. The RA will provide simple and standard instruction on how to use the equipment. The headset will then be placed on patient’s head and adjusted to ensure a comfortable and secure fit. Patients will be allowed to view the IVR module according to their age group (4–7 years, 8–12 years). During the intervention, the control of the IVR module will only be achieved by the head movement of the patients. The patients will also be told that the intervention will be discontinued if they experience motion sickness, eye discomfort, or headaches.

After receiving IVR intervention, the RA will invite the doctor/phlebotomist to start the venipuncture. The beginning of the procedure is indicated by doctor/ phlebotomist disinfecting the venipuncture site. The RA will note the time of first attempt at venipuncture. The end of the procedure is indicated by application of band aid to the venipuncture site. The RA will remove the IVR equipment from the child after the procedure. The protocol follows for the first venipuncture attempt only. If the first attempt is unsuccessful, additional attempts occurring after the protocol will be completed, but participants will be counted as unsuccessful case of the study.

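### The planned GEE is stated to be unbiased only if data are missing completely at random, an assumption the protocol does not defend; an analysis valid under missing at random is a cheap improvement

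*Protocol*

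**What the plan says.** Protocol, Data analysis: "The intention-to-treat principle will be adopted for the outcome comparisons between the intervention and control groups". Each outcome is compared across time points by GEE, which is said to "produce unbiased estimates even if there are missing data, provided that the data are missing at completely random". The section names no weighting, imputation or working correlation, and gives no reason why the condition should hold in this trial.

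Protocol, Sample size – Patients: "Taking into account of up to 15% attrition rate", the number is raised to 200 children. No reasons for attrition are given, and no split by arm.

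Protocol, Implementation Protocol: children in the immersive virtual reality (IVR) arm are told that "the intervention will be discontinued if they experience motion sickness, eye discomfort, or headaches". It is the IVR session that stops; nothing there says the child leaves the study or goes unassessed.

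Protocol, Data Collection Procedures: pain (Faces Pain Scale-Revised, FPS-R) and anxiety are taken 10 minutes before (T0), immediately after (T2) and 30 minutes after (T3) the procedure. Heart rate is taken at these times and at needle insertion (T1), and salivary cortisol at T0 and T3.

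**The concern.** Missing completely at random means that the chance of a missing value is unrelated to anything about the child, including scores already recorded. Missing at random is weaker: the chance may depend on recorded data, such as arm and earlier pain, but not further on the unseen value.

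In a hospital study whose last assessment comes 30 minutes after the procedure, a child who gives no rating or saliva sample may well be one who was upset or in pain. That is an inference, since the protocol gives no reasons for loss. If it is right, missingness is related to earlier recorded scores and the stated condition fails. The link could also differ by arm, because only one arm wears a headset. An unweighted GEE can then give a biased contrast, while a likelihood-based model or multiple imputation uses the recorded T0 and T2 scores to correct for it. The protocol has therefore tied its analysis to the stronger assumption when the same data allow a weaker one.

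**Working it through.** **1. The plan's own figures.** Inputs from Sample size – Patients: "detect a between-group difference of 0.8 in FPS-R scale", "with a pooled standard deviation of 1.84", "with 80% power at 5% level of significance". The two-sided test is stated in Data analysis.

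- Normal approximation: n = 2 × (1.96 + 0.84)² × 1.84² / 0.8² = 83.04, so 84 per arm.
- Two-sample t-test: 84.01, so 85 per arm, with 80.5% power.
- Attrition: 170 / (1 - 0.15) = 200.
- Failed first attempts: 200 / (1 - 0.20) = 250.

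All the stated numbers reproduce. The allowance for attrition protects power; it does nothing about bias.

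**2. When bias arises.** In one arm let m be the share missing and g the mean of the missing children minus the mean of those observed. The observed mean equals the full mean minus m × g, so

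observed contrast (IVR - control) = true contrast + m_C × g_C - m_I × g_I.

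- If g = 0 in both arms there is no bias, however unequal the rates. A simulation with 25% v 5% missing gave a difference of 0.80 against a true 0.80.
- If m × g is equal in the two arms the errors cancel.
- Bias needs m × g to differ between arms.

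**3. Illustration at T3.** All inputs are assumptions except the SD of 1.84, which is the protocol's. The scores are treated as normal.

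- Correlations: T0–T2 0.4, T0–T3 0.3, T2–T3 0.5.
- T2 mean 4 in control and 0.8 lower under IVR; true T3 effect -0.40.
- Pain-dependent missingness: logit(p) = -2.2 + 0.5 × (T2 pain - 4). Otherwise a flat 10%.
- A GEE with arm, time and arm-by-time and independence working correlation reduces, for this contrast, to the difference in observed means.
- The comparison method imputes T3 by regression on T0 and T2 within arm, which is valid under missing at random.

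| T3 missingness depends on T2 pain in | Missing, IVR / control | Independence GEE | Valid under missing at random |
|---|---|---|---|
| control only | 10% / 13% | -0.30 | -0.40 |
| both arms, same rule | 9% / 13% | -0.37 | -0.40 |

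Check of row 1: the missing controls scored about 0.77 points higher than the observed controls. So -0.40 + 0.13 × 0.77 = -0.30, an effect 25% too small. In row 2 the IVR arm has its own loss, which offsets most of this: 0.37 - 0.30 = 0.07. With dependence in the IVR arm only, the same arithmetic gives -0.40 - 0.07 = -0.47, so the bias can go either way.

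Sensitivity of row 1: a slope of 0.25 in place of 0.5 gives -0.36, a slope of 0.8 gives -0.23, and all correlations at 0.3 give -0.34.

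**4. Against the 0.8-point target.** Bias = 1.84 × (m_I × d_I - m_C × d_C), with d the missing-minus-observed gap in SDs.

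- 15% v 5% missing, gap 0.5 SD in both arms: 1.84 × (0.075 - 0.025) = 0.09, or 11.5% of 0.8.
- 15% v 5% missing, gap 1 SD in both arms: 1.84 × (0.15 - 0.05) = 0.18, or 23%.
- 15% in each arm, gap 1 SD in the IVR arm only: 1.84 × 0.15 = 0.28, or 34.5%.
- 15% in each arm, same gap in both: 0.

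**5. Scale.** With 125 children per arm and 10% and 13% missing, the standard error of the T3 difference is 1.84 × √(1/112.5 + 1/108.75) = 0.25. A bias of 0.10 is about 0.4 of a standard error.

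**The case against.** **The sentence is true.** It says the GEE is unbiased provided a condition holds, and that is the right condition for an unweighted GEE. A reader might infer that the protocol asserts the condition, or that unbiasedness will fail. Neither is supported: the claim is conditional, and nothing in the protocol links attrition to pain. This stands, and the point is limited to bias that may arise.

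**Planned attrition does not contradict the assumption.** The 15% is a planning ceiling taken from a cited study, and loss at that rate could be random. Unequal rates alone do no harm either (step 2). This stands.

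**Stopping IVR is not missing data.** A reader might take motion sickness, eye discomfort and headache as arm-specific dropout. The text stops the IVR session only, the analysis is by intention to treat, and T2 and T3 are scheduled for all participants. This stands. It leaves only a request to say so plainly.

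**The illustration is favourable to the concern.** Most of the bias comes from letting the arms differ, it is shown at T3 only, and the independence structure is assumed because the protocol names none. A well-chosen working correlation would reduce it. All true. No bias at T2 has been demonstrated; for T2 to be biased, missing T2 ratings would have to depend on pain or distress differently by arm.

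**The statistical analysis plan may deal with it.** It is not shown, so the absence of sensitivity analyses or imputation details is not held against the protocol. What remains is a method and an assumption that the protocol states itself.

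A reader might also add the 20% of failed first attempts and speak of 1 - 0.80 × 0.85 = 32% missing. The protocol does not say whether those children are assessed or analysed, so that is a separate question and is not counted here.

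**Conclusion.** The point holds as a weakness in a stated choice, not as an error of fact. The analysis is tied to missing completely at random, the protocol does not defend that assumption, and it plans for up to 15% attrition. If missing T2 or T3 values depend on earlier pain or distress, and differently by arm, the GEE contrast may be biased in either direction.

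For a true T3 effect of -0.40 with about 10% to 13% missing, the independence GEE gives about -0.30 when one arm's missingness depends on T2 pain and about -0.37 when both arms' does; a method valid under missing at random gives about -0.40. These sizes rest on assumed correlations, means and missingness rules that the protocol does not supply, and on an independence working correlation. The recovery to -0.40 also assumes that missingness depends only on recorded scores. With little missing data, or similar mechanisms in both arms, the bias would be small.

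**What to change.** For the repeated outcomes choose one of two:

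- a likelihood-based mixed model for repeated measures with arm, time, arm-by-time, age stratum and baseline value, and unstructured covariance; or
- the planned GEE after multiple imputation done separately by arm, using T0 and T2 scores, heart rate and age.

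Imputation is the more useful route for cortisol, which has no value between T0 and T3 to borrow from.

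Replace the sentence on missing completely at random with a statement that the analysis assumes missing at random given the variables in the model. Add one sentence that children who stop IVR still give T2 and T3 assessments and are analysed in their assigned arm.

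Cost: a change of wording and somewhat more analysis work, with no new data and no more children. In exchange, the result relies on a model for the outcome or for the imputation, and missing at random cannot itself be verified from the data.
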